#### Other outcome measures

Association between the donors’ and recipients’ dietary profile and microbiome.Time, that is, number of days, from donor stool processing to treatment for association between efficacy and freezer life of FMT.

### Donor sample acquisition and processing

Donors will be recruited following advertisement from healthy unrelated anonymous individuals living in Birmingham. We are excluding healthcare workers due to their potential exposure to microbes affecting the microbiome. Donors must be ≥18 and<50 years of age, have a normal morning bowel habit, have a normal body mass index (≥18.5 and ≤25), be non-smokers (not smoked for at least 12 months) and have no recent history of diarrhoea or rectal bleeding. Potential donors will undergo rigorous screening using a health-screening questionnaire. Those who are eligible following this screening will be consented for the donation process and have blood and faecal samples taken to test for transmissible pathogens in accordance with UK, American Gastroenterology Association (AGA) and European guidelines.^19–21^Individuals who pass the screening process will be invited to donate morning faecal samples for 10 days and to deliver these for processing within 6 hours of defaecation. At first donation, they will also be asked to complete the EPIC-Norfolk food frequency questionnaire.^22^

Donations will be processed and stored under an MHRA manufacturing licence at the University of Birmingham Microbiome Treatment Centre. Stool collection and processing were performed under aerobic conditions. Donations will be prepared in saline with 10% glycerol added as a cytoprotectant. Samples will then be stored frozen at −80°C for up to 24 weeks. Samples will be dispatched for use at each site as required. An aliquot from each donated sample will be kept for analysis in the event of AEs occurring as a result of FMT and samples from each donation period will be sent for genetic sequencing and metabolic analysis. At the end of each 10-day donation period, donors will receive financial compensation and will undergo an exit health questionnaire and be asked to provide a further stool sample to test for pathogens. Further information on the donor sample processing will be present in the protocol and a laboratory standard operating procedure (SOP) for donor preparation (available on request).

### Participants

#### Inclusion criteria

Adult patients (aged between 16 and 70 years) with clinically confirmed UC for at least 12 weeks prior to the screening visit.Partial Mayo score of ≥4 and≤8 despite stable disease maintenance treatment with 5-aminosalicylates with or without immunomodulators, or on no treatment.Rectal bleeding subscore of ≥1 on the partial Mayo;.Able to give written, signed informed consent.

#### Exclusion criteria

Stool positive for *Clostridium difficile* or infection by either PCR or ELISA.Positive for Hepatitis A/B/C and/or HIV infection.Antibiotics in the preceding 12 weeks prior to date of the screening visit.Systemic/topical steroids in the preceding 2 weeks prior to the date of the screening visit.Biologics in the preceding 12 weeks prior to the date of screening visit.Commercial probiotics and prebiotics in the preceding 12 weeks prior to the date of the screening visit.On oral nutritional supplements or enteral/parenteral nutrition in the preceding 4 weeks prior to the date of the screening visit.Pregnant or lactating.Not willing to take appropriate contraceptive measures to prevent pregnancy during trial participation.

### Participant enrolment

Potentially eligible patients who express an interest in participating in the trial will be consented via a two-stage consent process. Participant information sheets will be provided to facilitate the consent process.

#### Registration and screening visit

The first stage will involve consent for trial-specific screening activities, and consent to collect stool and urine samples for the mechanistic substudies. Patients will undergo basic physiological assessments (pulse, blood pressure, temperature, height and weight) and baseline blood tests. They will be provided with a diary to record bowel symptoms (so that the partial Mayo score can be calculated at the randomisation visit), stool sample kits and bowel preparation kits (Moviprep). They will be asked to return the *C. difficile* stool sample as soon as possible, so that the result is available prior to the randomisation visit.

Following the screening visit, the qualitative researcher will arrange for an interview with the patient to take place prior to their randomisation visit (see Randomisation visit below). The research team at the hospital will contact the patient to notify them of their stool result. If they tested negative for *C. difficile*, they will be invited to attend the randomisation visit. Instructions will be given on when to take the bowel preparation, and they will be asked to collect a stool sample on the same day prior to taking the bowel preparation, which they will bring to the randomisation visit.

#### Randomisation visit

The second stage is consent for entry into the trial. Following confirmation of all eligibility criteria and consent to randomisation, basic physiological assessments will be undertaken, blood test results will be checked, a urine sample will be taken for pregnancy testing in women and metabolomics and the partial Mayo score will be calculated from diaries. The patient will be asked to complete the baseline QoL questionnaires—IBDQ and SF-36. All patients will have a colonoscopy to assess disease (done after randomisation), so that a full Mayo score can be calculated, and to collect mucosal biopsies.

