### Interventions

Before the initial FMT treatment, all patients will receive standard bowel preparation: 2 L of reconstituted Moviprep solution within the 24 hours prior to procedure.

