### Data collection

All patients will be followed weekly up to week 8, and then again at week 12. At each visit, the partial Mayo score will be calculated from the patient diaries, and medication use and any adverse events occurring will be recorded. Stool samples will be collected at weeks 2, 4, 6, 8 and 12, and blood samples will be taken for CRP assessment at weeks 4, 6 and 8. At weeks 8 and 12, physiological data, a urine sample and the SF-36 and IBDQ QoL questionnaires will also be collected. At week 8, a flexible sigmoidoscopy will be undertaken to calculate the full Mayo score (see online supplementary figure 1).

10.1136/bmjopen-2019-030659.supp2Supplementary data

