### STOP/GO guidelines

At the end of the pilot, the IOC will be convened to review the data. This group will make a recommendation to the Trial Management Group on (1) which route (if any) of FMT is appropriate to take forward to the full trial and (2) whether it is feasible to proceed to the full RCT.

To determine whether we will proceed forward to the main RCT, a pragmatic review of the pilot data in terms of assessing treatment efficacy (based on clinical response), tolerability and patient acceptability will be undertaken. STOP/GO guidelines will be used to determine whether to proceed forward to the main RCT, and we propose then to take forward the preferred method of FMT delivery into a randomised double-blind placebo-controlled trial with a clinical efficacy outcome (clinical remission).

The first STOP/GO decision will be on which route of FMT to take forward to the full RCT. The pilot is not powered to show differences in the two modes of delivery (NG or COLON); therefore, a decision or recommendation on which route to use in the main trial requires expert judgement and cannot be made based on a purely numerical process. The following data will be reviewed by the IOC:

The proportion of patients who achieve a clinical response following FMT by the NG route (A threshold of achieving a clinical response in around 40% of patients treated may be used. This threshold will be agreed after discussions by the Trial Management Group and the IOC prior to any data analysis being performed).The proportion of patients who achieve a clinical response following FMT by the COLON.Whether FMT by either route is associated with a change in faecal calprotectin.Whether FMT by either route is associated with changes in the colonic microbiome and metabolome.Tolerability and safety for each route.Patient acceptability of FMT by the NG route through the qualitative interviews (including advantages and disadvantages of the NG route).Patient acceptability of FMT by the COLON route through the qualitative interviews (including advantages and disadvantages of the COLON route).

Following review of the above data, whether the IOC can recommend a route to take forward to the main trial, will form the basis of the first STOP/GO decision.

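### The baseline urine for metabolomics is taken after the bowel preparation, so within-route change in the urinary metabolome, at least to week 12, mixes recovery from the preparation with any FMT effect

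*Protocol article*

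**What the plan says.** The relevant statements in the protocol article are spread over several sections.

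- Registration and screening visit: patients leave with "stool sample kits and bowel preparation kits (Moviprep" and are told when to take the preparation. For the baseline stool, "they will be asked to collect a stool sample on the same day prior to taking the bowel preparation". Consent for stool and urine collection is obtained at this stage.
- Randomisation visit: "a urine sample will be taken for pregnancy testing in women and metabolomics". The colonoscopy that provides the full Mayo score and the baseline biopsies follows randomisation.
- Interventions: before the first FMT, "all patients will receive standard bowel preparation: 2 L of reconstituted Moviprep solution within the 24 hours prior to procedure". The NG treatment and COLON treatment sections both place the first FMT on the day of randomisation.
- Data collection: "At weeks 8 and 12, physiological data, a urine sample and the SF-36 and IBDQ QoL questionnaires will also be collected". A flexible sigmoidoscopy is done at week 8; no endoscopy is listed for week 12.
- Mechanistic outcome measures: the urinary metabolome is a named outcome.
- STOP/GO guidelines: among the items that the Independent Oversight Committee (IOC) reviews is "Whether FMT by either route is associated with changes in the colonic microbiome and metabolome".

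**The concern.** A change score is interpretable only if the two samples differ in the factor of interest and not in some other systematic way. For stool the plan takes care of this by sampling before the bowel is emptied. For urine it does not: the baseline sample follows the preparation, and the week 12 sample is taken with no preparation scheduled.

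This matters because of how the urine data may be read. The mechanistic objective concerns changes induced by FMT via each route, and the IOC item asks whether either route is associated with change. Both are within-route questions, answered against baseline with no untreated group. Any return of the urinary metabolome to its unprepared state would appear as change in both routes and could be credited to FMT.

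**Working it through.** The article gives no figure on this point to reproduce, so the check is mainly of sequence.

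**Order of events at baseline.** (1) Preparation kits are handed out at screening. (2) Baseline stool is collected. (3) The 2 L preparation is taken, within 24 hours of the procedure. (4) At the randomisation visit, the metabolomics urine is collected. (5) Colonoscopy, biopsies and first FMT follow on the same day. No clock times are given, but as scheduled the urine comes after the preparation.

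**Baseline against follow-up, by sample type.**

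| Sample | Baseline | Follow-up | Like with like? |
|---|---|---|---|
| Stool (16S, SCFA) | Before preparation | 16S: weeks 2, 4, 6, 8, 12; SCFA: weeks 8, 12 | The baseline problem does not arise |
| Urine, week 12 | After preparation | No procedure or preparation scheduled | No |
| Urine, week 8 | After preparation | Sigmoidoscopy; preparation not stated | No, unless week 8 was prepared similarly |
| Mucosal biopsies, week 8 | After preparation | Sigmoidoscopy; preparation not stated | Depends on week 8 preparation |

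**Between routes.** Write the baseline-to-follow-up change in route r as FMT effect(r) + P, where P is the preparation component. All patients take the same preparation, so P is the same in expectation in both routes. The within-route change carries P in full. The NG minus COLON difference is FMT effect(NG) + P − FMT effect(COLON) − P, and P cancels.

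**Illustration of size.** Inputs: n = 15 per route (the cohort size in the STOP/GO guidelines); FMT effect = 0; P = d standard deviations of the paired change. The value of d is assumed and comes from no document. With 14 degrees of freedom and noncentrality d × √15, the probability that a two-sided 95% paired-t interval excludes zero is

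1 − F(t; 14, d√15) + F(−t; 14, d√15),

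where F is the noncentral t distribution function and t is the 97.5% point of the central t with 14 degrees of freedom. The figure for both routes is the square of the figure for one.

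| Assumed d | One given route | Both routes |
|---|---|---|
| 0 | 0.050 | 0.003 |
| 0.2 | 0.112 | 0.012 |
| 0.3 | 0.192 | 0.037 |
| 0.5 | 0.438 | 0.192 |
| 0.8 | 0.821 | 0.675 |
| 1.0 | 0.949 | 0.901 |

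These are properties of a paired interval at n = 15 under any common shift. They show what a shift of a given size would do, not that one of that size exists.

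**The case against.** The strongest case against the point has five parts.

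- *The main data are protected.* This stands. Faecal 16S and faecal SCFA rest on stool, and the only baseline stool described is collected before the preparation. The IOC item concerns the colonic microbiome and metabolome, which stool addresses directly. A reader might infer that the microbiome and metabolome results as a whole are compromised; the documents do not support that.
- *Biopsies taken at colonoscopy must follow preparation.* This stands too. A reader might infer that mucosal change has the same fault as urine. That holds only if preparation before the week 8 sigmoidoscopy differed from baseline. The condensed article does not say, and its visit figure is in a supplement that is not shown. That silence is not itself a fault.
- *The size is unknown and there is no significance rule.* Correct. Analysis of outcome measures excludes formal hypothesis testing, and the STOP/GO guidelines call for expert judgement on several kinds of evidence. The percentages above are illustrative.
- *The choice of route is a comparison of NG with COLON.* A shared preparation effect cancels there in expectation. The point bears only on whether change occurred within a route.
- *Without an untreated arm, within-route change cannot be attributed to FMT alone in any case.* True, and moving the urine would not cure that. But this particular source of change is systematic, tied to the baseline sample and easily avoided, as the plan already does for stool.

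What remains after these concessions is the urine: a named outcome whose baseline and week 12 samples are taken under different conditions.

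**Conclusion.** The point holds for the urinary metabolome. As scheduled, all 30 baseline urine samples are post-preparation and the week 12 samples are not, so within-route change to week 12 mixes recovery from the preparation with any FMT effect. The same applies to week 8 unless patients were similarly prepared for the sigmoidoscopy. Mucosal change is affected only on that same condition.

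The conclusion rests on the stated visit sequence and on the possibility that the preparation alters urinary metabolites. The documents give neither the size nor the duration of such an effect, so the bias is possible rather than demonstrated. The consequence is limited: the faecal results, the between-route contrast and the other items before the IOC are untouched. It merits correction because the remedy is specific and nearly free.

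**What to change.** **Main RCT.** Collect the baseline metabolomics urine together with the pre-preparation stool, and keep the visit-day urine for the pregnancy test. Consent for urine is already obtained at screening, so this costs one sentence in the visit schedule and a urine container in the kit.

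**Pilot.** The article states that recruitment closed in April 2019 and that analysis was to start in August 2019, so only analysis and reporting can change:

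- Base the IOC's within-route microbiome and metabolome item on stool, with its pre-preparation baseline.
- Report the urinary metabolome as NG versus COLON differences at weeks 8 and 12.
- Label within-route urinary change as confounded with bowel preparation.
- State whether patients were prepared before week 8 sampling; if this differed from baseline, apply the same label to mucosal change.
- Reconcile the SCFA matrix: Mechanistic outcome measures lists SCFA under the urinary metabolome, while the section on bacterial metabolites specifies the SCFA assay on faecal samples. Which matrix carries the outcome decides how much the urine timing matters.

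The cost is wording in the analysis and report. The downside is that within-route urinary change can no longer be presented as induced by FMT.

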### Randomisation

Patients will be randomised at the level of the individual in a 1:1 ratio to either NG or COLON delivery of FMT. Randomisation will be provided by a computer-generated program at the Birmingham Clinical Trials Unit. A minimisation algorithm will be used to ensure balance in the treatment allocation over the following variables:

Partial Mayo score (4–5 or 6–8).Current smoking status (current smoker: yes or no (not smoked for the past 12 months)).

A ‘random element’ will be included in the minimisation algorithm, so that each patient has a probability (unspecified here), of being randomised to the opposite treatment that they would have otherwise received.

### Interventions

Before the initial FMT treatment, all patients will receive standard bowel preparation: 2 L of reconstituted Moviprep solution within the 24 hours prior to procedure.

#### NG treatment

Patients randomised to NG treatment will be pretreated with a proton pump inhibitor (lansoprazole 30 mg) and a prokinetic agent (domperidone 10 mg) at least 30 min prior to each FMT infusion to reduce gastric acid secretion and prevent the risk of gastro-oesophageal regurgitation. Naso-gastric tubes (NGTs) will be positioned and checked for correct position as per local protocol. Following thawing at room temperature, 50 mL thawed FMT containing 30 g faeces will be infused. Following the first treatment, patients will return for the next 3 days for further treatment following an overnight fast. It will be the individual’s choice whether they wish to retain the NGT for the 4-day treatment course or have the tube removed and repassed every day. On the last day of treatment, the NGT will be removed to be replaced for the second course of treatment. At week 4, patients will return for a further four FMT infusions over 4 consecutive days following a fast from midnight.

In summary, patients will receive 30 g FMT in 50 mL aliquots for NG administration each day for 4 days at the start of the trial (starting on the day of randomisation), and then again for 4 days in week 4 (total FMT dose 240 g).

#### COLON treatment

Patients randomised to COLON treatment will receive a thawed 250 mL aliquot of FMT (containing 150 g faeces) on the day of randomisation. This will be delivered to the colon using a spray catheter, with 125 mL sprayed into the caecum to treat the right side of the bowel and the remaining 125 mL sprayed directly onto the rest of the colon. Following treatment, patients will receive a single dose of loperamide. Patients will return on a weekly basis to receive 100 mL enema up to week 7 containing 50 mL of saline and 30 g faeces, followed by loperamide each time.

In summary, patients will receive 150 g of stool in 250 mL for colonic administration on the day of randomisation followed by 30 g of stool in 100 mL in normal saline for administration by enema for 7 weeks (total FMT dose 360 g).

### Data collection

All patients will be followed weekly up to week 8, and then again at week 12. At each visit, the partial Mayo score will be calculated from the patient diaries, and medication use and any adverse events occurring will be recorded. Stool samples will be collected at weeks 2, 4, 6, 8 and 12, and blood samples will be taken for CRP assessment at weeks 4, 6 and 8. At weeks 8 and 12, physiological data, a urine sample and the SF-36 and IBDQ QoL questionnaires will also be collected. At week 8, a flexible sigmoidoscopy will be undertaken to calculate the full Mayo score (see online supplementary figure 1).

10.1136/bmjopen-2019-030659.supp2Supplementary data

### Timelines

We completed recruitment into this pilot study in April 2019. Data collection will be completed by July 2019 and analysis of the data will commence in August 2019.

### Qualitative research: patient and clinician experience and acceptability of FMT and trial processes

A comparison of the acceptability of the two routes of FMT being used in this study is key to the outcome of this pilot study. A qualitative researcher will conduct interviews with patients participating in both arms of the trial. Each patient will take part in a semistructured interview at two time points; following the screening visit prior to randomisation and after the 12-week follow-up visit. These one-to-one interviews will take place either in person, by telephone or Skype, as preferred by the patients. The initial interview will focus on participants’ experience of UC and treatment to date, along with their understanding and expectations for FMT and the pilot study. A background questionnaire collecting sociodemographic and clinical details will also be administered. During the follow-up interview, patients’ actual experience within the pilot study, including that of FMT (by NG and COLON) and of related trial processes and procedures will be explored. Interviews will also gather data on patient perspectives regarding important impacts and outcomes of FMT, thus providing the opportunity to compare these with the outcome measures selected for inclusion in the pilot and (later) full RCT. Further interviews with patients who withdraw from FMT treatment early and with a small sample of patients who decline consent to participate following screening (should this happen), will provide in-depth understanding of these decisions. Interviews will also be conducted with staff at the pilot sites to review their experience of trial conduct, for example, the acceptability and logistics of complex trial procedures within clinical environments. Interviews schedules can be found in online supplementary file 1.

Data from this qualitative research will contribute to an assessment of patient and clinician experience and acceptability of FMT within the pilot context, and along with recruitment and dropout rates, and data regarding clinical response, this will inform a decision about whether the NG or COLON route of delivery is taken forward to the full RCT. The qualitative data will also contribute to the refinement and optimisation of trial processes prior to the full RCT.

#### Analysis of qualitative data

Interviews will be recorded with the consent of participants and transcribed clean verbatim for analysis. Analysis will be conducted with reference to recordings, transcripts and field notes taken at the time of data collection. A thematic analysis of content will be informed by the framework analytical approach.^23^ Following initial familiarisation with the interview data, development of thematic frameworks and data coding will proceed in an iterative manner. Data collection and analysis will run concurrently so that emergent analytical themes can inform further data collection, and in particular comparative analytical questioning between patients allocated to NG or COLON.

